### Data management

When the data collection is completed, all paper data will be converted into electronic data according to the case report form (CRF). All data will be independently recorded by two researchers ([name], [name]) using the EpiData software version 3.1. The software automatically checks inconsistent or questionable data according to the check results, and generates the data question form (DQF), which is handed over to the investigator for review. After all the data are confirmed, checked, and stored in an electronic database, the identifiable information (e.g., real name) of the participants will not appear in the relevant reports of the trial to protect their privacy. Only researchers directly involved in the analysis of the RCT will have access to the final trial data set, which will only contain coded data.

### Data analysis

Demographics and other characteristics will be reported descriptively to summarize the distribution of all variables via the statistics software (SPSS 24.0). The means and SD will be calculated for continuous normally distributed variables and medians and ranges for non-normally distributed variables. Categorical variables will be presented by absolute numbers and percentages. All cases for both baseline and follow-up measurements will be analyzed for the different outcomes. If missing values exceed 10%, we will impute missing values on covariates by using multiple imputation.

According to the intention-to-treat principle, we will compare the number of patients showing post-intervention 7-point improvement in the PCI scores between the intervention group and the control group using Fisher’s exact tests. A linear mixed-effect model for repeated-measures analysis will be used to analyze the changes in cognition such as treatment, time point, and the interaction between treatment and time point. The between-group effect size will be calculated in post-treatment means (dividing the between-group difference with the pooled standard deviation). The effect sizes of 0.20, 0.50, 0.80, and 1.30 represent small, medium, large, and very large effect, respectively [41]. Two-sided significance level for all tests is 0.05.

Linear regression analysis adjusted for baseline will be used to assess the association between changes in cancer-related symptoms (fatigue, anxiety, and depression) and changes in cognitive function. Adherence to the Baduanjin exercise will be noted by adherence rate ((total frequency − absenteeism)/total frequency × 100%).

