**Method:**

A single-blinded, randomized control trial was designed. The trial will recruit 70 patients with early-stage breast cancer scheduled to receive chemotherapy from Shanghai in China. All participants will be randomly assigned to (1:1) the supervised Baduanjin group (5 times/week, 30 min each time) or the wait-list control group for 3 months. The effect of Baduanjin exercise intervention will be evaluated by outcome measures including subjective and objective cognitive function, symptoms (fatigue, depression, and anxiety), and health-related quality of life at pre-intervention (T0), 8 weeks (T1), and 12 weeks (T2). The PCI score in the FACT-Cog as the primary cognitive outcome will be reported descriptively, while effect sizes and 95% confidence intervals (CIs) will be calculated. The collected data will be analyzed by using an intention-to-treat principle and linear mixed-effects modeling.

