### Sample size

The sample size was estimated in this study by using perceptive cognitive impairment as the main effect indicator, which refers to the results of Oh et al. [26]. Using the G*Power 3.1 software, 58 cases of the total sample can be calculated with a test power of 0.80. Considering the 20% dropout rate, the total sample size for this study is about 70 patients randomized to the intervention group or the control group.

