### Data collection

All the data will be collected from participants, including those who discontinue the intervention. Most of the outcome data will be collected via the provided paper-and-pencil measures (anonymised by participant ID). If participants are interested in electronic measures (anonymised by participant ID), these will be provided.

The cognitive assessors will conduct a comprehensive training in scoring the measures. Interrater reliability will be determined, and discrepancies will be resolved by consensus. After participants have been randomized, dropout and premature termination from the two groups at any point will be recorded along with relevant reason. Participants can choose to withdraw and will not be affected at any time while declining to participate or withdrawing from the trial. In some cases, participants will discontinue the intervention, such as illness, progression of their disease, or inability to engage despite adjustment of the program. Participants who are withdrawn from the intervention during the trial will not continue to follow-up but will not be replaced.

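### The 7-point responder test is labelled intention-to-treat, but the only imputation rule covers covariates and nothing stated handles a missing follow-up PCI score

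*Protocol article*

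**What the plan says.** All references are to the protocol article.

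- **Data analysis, imputation:** "If missing values exceed 10%, we will impute missing values on covariates by using multiple imputation". No other imputation rule is given.
- **Data analysis, cases analysed:** "All cases for both baseline and follow-up measurements will be analyzed for the different outcomes".
- **Data analysis, responder test:** "According to the intention-to-treat principle, we will compare the number of patients showing post-intervention 7-point improvement in the PCI scores", by Fisher's exact test. No denominator is stated, and nothing says how a patient without a follow-up PCI score is classified.
- **Data analysis, repeated measures:** "A linear mixed-effect model for repeated-measures analysis will be used to analyze the changes in cognition", with treatment, time point and their interaction. The Abstract ties intention-to-treat to this model as well: "The collected data will be analyzed by using an intention-to-treat principle and linear mixed-effects modeling".
- **Sample size:** 58 patients are raised to about 70, "Considering the 20% dropout rate".
- **Data collection:** the section opens with "All the data will be collected from participants, including those who discontinue the intervention" and closes with "Participants who are withdrawn from the intervention during the trial will not continue to follow-up but will not be replaced".

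**The concern.** A patient can be classed as a 7-point improver only if both the T0 and the post-intervention PCI scores are known. The plan foresees that a fifth of patients will drop out, and one of its two statements on data collection ends follow-up for those withdrawn from the intervention. The imputation rule does not reach the score that will then be missing. For this test, the stated rule is aimed at the wrong variable.

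Two things are at stake. First, if the test is run on observed scores, the compared proportions are conditional on having stayed in follow-up. The reasons that the Data collection section gives for discontinuing (illness, disease progression, being unable to engage even after adjustment) are related to health. The last could arise mainly in the exercise arm, because controls have no exercise program to stop during the study. Second, while the denominator is open, it can be chosen after the data are seen, and that choice can decide which side of 0.05 the result falls on.

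**Working it through.** **Inputs from the article.** Total 58 before dropout and about 70 after; dropout 20%; 1:1 allocation, so 35 per arm; two-sided level 0.05; responder threshold 7 PCI points.

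**Assumptions.** Responder counts and the split of losses between arms are assumed, because the article gives neither. The post-intervention score is taken to be T2.

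**Step 1: the plan's own figure.** 58 × 1.20 = 69.6, rounded to 70, which matches. The 58 cannot be recomputed, because no effect size or SD is given.

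**Step 2: how many scores will be missing.** 0.20 × 70 = 14 missing and 56 observed, or 28 per arm if losses are equal. The margin actually built in is 70 − 58 = 12, so 12 to 14 patients is a fair range.

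**Step 3: does the handling of these patients matter?** Fisher's exact test, two-sided:

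| Assumed loss (exercise, control) | Handling | Exercise | Control | Difference | p |
|---|---|---|---|---|---|
| 7, 7 | observed scores only | 14/28 | 6/28 | 28.6 points | 0.0496 |
| 7, 7 | missing = not improved | 14/35 | 6/35 | 22.9 points | 0.063 |
| 7, 7 | all missing controls improved | 14/35 | 13/35 | 2.9 points | 1.00 |
| 7, 7 | all missing exercise patients improved | 21/35 | 6/35 | 42.9 points | 0.0005 |
| 11, 3 | observed scores only | 12/24 | 7/32 | 28.1 points | 0.045 |
| 11, 3 | missing = not improved | 12/35 | 7/35 | 14.3 points | 0.28 |

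The third and fourth rows are extreme bounds, not plausible results. Counting the missing as not improved is not neutral either: when more exercise patients are lost, it works against exercise. The table shows only that the unstated rule can decide the result.

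**Step 4: possible bias without a true effect.** Suppose 30% improve in both arms, a fraction m of the exercise arm is lost, all of those lost are non-improvers, and loss in the control arm is unrelated to response. The observed exercise rate is then 0.30 / (1 − m):

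- m = 0.10: 0.333, a spurious difference of 3.3 points
- m = 0.20: 0.375, a spurious difference of 7.5 points
- m = 0.30: 0.429, a spurious difference of 12.9 points

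This is a one-sided scenario. If both arms lose similar patients at similar rates, most of the difference cancels.

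**Step 5: which analyses are touched.** The responder test needs both scores, so it is touched. A likelihood-based mixed model over T0, T1 and T2 is not touched in the same way: a patient with T0 and T1 but no T2 still contributes, and no outcome imputation is needed under missing at random.

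**The case against.** **A reader might infer that the responder test is in fact a completers' analysis.** The text does not support that as a statement of fact. The sentence on cases analysed, "All cases for both baseline and follow-up measurements will be analyzed for the different outcomes", can mean only patients with both measurements, but it can also mean all patients at both times. Comparing a number of patients fits a denominator of all randomized, with the missing counted as not improved. What stands is that no rule is fixed and that the label has nothing behind it.

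**A reader might extend the criticism to the whole analysis.** That fails too. The mixed model is already planned and can use the available visits. Its limit is the missing-at-random assumption, which loss through illness or progression may strain.

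**A reader might say that the covariate rule has no use.** It has one: the regression of change in cognition on change in fatigue, anxiety and depression has predictors that dropout will leave missing.

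**Denominators and sensitivity analyses are commonly left to a SAP.** The Trial monitoring section mentions one that is not shown. Silence alone would not be a finding. Here, however, the article states a missing-data rule, restricts it to covariates, and attaches an intention-to-treat label to a test that the rule does not serve.

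**The trial is called a pilot, and the Abstract has PCI reported descriptively with effect sizes and intervals.** This lowers the stakes of any one p-value, but the responder test is still planned at the 0.05 level. It is also fair that imputation with about 28 observed patients per arm must rest on few predictors, and that differential loss by arm is plausible rather than shown.

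**Conclusion.** The point holds for the Fisher responder comparison and not beyond it. About 14 of 70 patients (20%) can be expected to lack a final PCI score, the only imputation rule leaves that score out, and no other rule retains these patients. If the test is run on observed scores, it is an observed-case comparison and should not be called intention-to-treat. The size of any bias cannot be derived from the article, which gives no responder rates. The shifts in p (0.0496 to 0.063, and 0.045 to 0.28) and the spurious differences of 3.3 to 12.9 points rest on assumed counts and loss patterns and should be cited as such. The count of 14 assumes that those who drop out have no later PCI score, which is what one of the two conflicting data-collection sentences implies. The plan should be changed, since PCI is the primary outcome and the loss is foreseen.

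**What to change.** 1. For the responder test, remove the 10% trigger and the restriction to covariates. Multiply impute missing PCI scores by arm, using T0 and T1 PCI and a small set of the symptom scores already collected (for example fatigue and HADS). Derive 7-point response after imputation, with all randomized patients as denominator, and pool the risk difference by Rubin's rules.
2. Add one sensitivity analysis, named in advance: either missing counted as not improved, or imputed PCI scores shifted by a stated delta.
3. Keep the linear mixed model on all available PCI values as the main analysis, and state its missing-at-random assumption.
4. Reword the sentence on which cases are analysed so that it has one meaning.
5. Reconcile the two Data collection sentences on whether data are collected after a patient discontinues or is withdrawn from the intervention.

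The cost is a little more analysis work and a pooled estimate with an interval in place of a single Fisher p-value. The imputation model must stay small for the sample. No extra patients or assessments follow from items 1 to 4; what item 5 costs depends on how the two sentences are reconciled.

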### Inclusion criteria

The inclusion criteria meeting this study are as follows:
Female patients newly diagnosed with stage I to III breast cancerScheduled to receive adjuvant chemotherapyAged 40 to 75 yearsUsing WeChatSufficient fluency of the Chinese languageWilling to participate in the study and be randomly assigned

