### Study assessments

Cognitive ability and several patient-reported outcome (PRO) questionnaires will be collected as primary outcome and secondary outcomes, respectively. These outcome assessments will be carried out by professional researchers at pre-intervention (T0), 8 weeks (T1), and 12 weeks (T2) during intervention. The most important primary outcome is cognitive ability, which is assessed using Cancer Therapy-Cognitive Function (FACT-Cog). If there is a 7-point improvement in the FACT-Cog PCI score between the groups, then the intervention will be thought to have tended to have a beneficial effect based on minimal clinically important difference (MCID) [32]. Demographic information collected via interview pre-intervention include patients’ age, level of education, and economic status. Disease information is retrieved from medical records by two trained study coordinators ([name], [name]). The schedule of study outcome assessments is outlined in Fig. 2.

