## Discussion

Currently, although cognitive decline is a well-known phenomenon, there are no pharmacological interventions to prevent or alleviate cognitive problems in patients with various non-central nervous system cancers. Physical exercise has been recommended as a part of rehabilitation, which appears to be a feasible and promising non-drug intervention that improves cognitive abilities. Preclinical study [42] has shown that low-intensity exercise may assist in preventing cognitive dysfunction in chemotherapy-exposed patients with breast cancer. Baduanjin exercise as a mind-body therapy has beneficial effects on fatigue, quality of life, and negative mood among patients [30, 43, 44]. In addition, this kind of exercise is easy to learn and can be widely used in the community with no limitation for the environment [45]. Meanwhile, there is evidence demonstrating improved attention of the elderly or patients with MC [46, 47]. In light of the previous literatures, we hypothesized that the exercise program may have a protective effect on the cognitive function of breast cancer survivors. Given ethical reasons, patients assigned into the control arm have the opportunity to carry out a 3-month exercise program after completion of the study, so as to decrease subsequently the risk of sample contamination. If Baduanjin exercise seems to be effective, it may provide evidence-based intervention during cancer treatment to possibly minimize or decrease cognitive problems, thereby improving patients’ quality of life. Previous preclinical and human studies have shown that a wider range of chemotherapy was associated with cognitive changes in cancer patients, so we hope that the results of this study will also be applicable to patients with other types of tumors during receiving chemotherapy. Therefore, the ultimate purpose of this study may have a positive impact on the quality of life or physical and mental health of the growing survivors with cancer.

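### The 7-point PCI criterion is a between-group difference in one section and a per-patient responder cut-off in another; the responder test suits a protective aim poorly and loses power

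*Protocol article*

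**What the plan says.** The protocol article handles the primary outcome, the FACT-Cog PCI score, in several ways.

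- **Study assessments** sets the criterion for benefit at group level: "If there is a 7-point improvement in the FACT-Cog PCI score between the groups, then the intervention will be thought" to tend towards benefit, with 7 points described as the minimal clinically important difference.
- **Data analysis** applies 7 points to individuals. Its sentence on intention-to-treat reads: "we will compare the number of patients showing post-intervention 7-point improvement in the PCI scores between the intervention group and the control group". The test it names for this is Fisher's exact test. The same paragraph then plans a linear mixed-effects model with treatment, time and their interaction, and a standardised difference in post-treatment means. It adds "Two-sided significance level for all tests is 0.05". No order of priority is given.
- **Abstract (Method)** says PCI will be reported descriptively with effect sizes and 95% confidence intervals, and names intention-to-treat together with mixed modelling. It does not mention the responder comparison.

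On the aim, the Discussion states "we hypothesized that the exercise program may have a protective effect on the cognitive function of breast cancer survivors", and the Abstract's Background also speaks of protection. The list of aims at the end of the Background section asks whether cognitive function improves. The first eligibility criterion begins "Female patients newly diagnosed with stage I to III breast", and no cognitive complaint is required for entry. Baseline is taken within 3 days of starting chemotherapy (Interventions).

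**The concern.** A 7-point difference between arm means and a difference in the number of patients who each gain 7 points are separate estimands. One cannot be read off the other without knowing the spread of change scores and the average change in controls, and the article gives neither. A reader therefore cannot tell which result would meet the trial's own criterion for benefit.

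The responder version also fits the protective hypothesis poorly. If exercise works by preventing decline, its success is a woman whose PCI stays level while it would otherwise have fallen. The improver count scores her as a failure, together with the women who decline. Finally, cutting a continuous score in two and applying Fisher's test in a trial of about 70 patients discards information that the mixed model would use. If the Fisher result were taken as the verdict, a real effect could more easily be missed.

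**Working it through.** **The plan's own figure.** The Sample size section says "58 cases of the total sample can be calculated with a test power of 0.80" and "Considering the 20% dropout rate, the total sample size for this study is about 70 patients". It states no effect size, SD, responder rate or test, so 58 cannot be reproduced from stated inputs. Solving backwards, a two-sided two-sample t-test at 0.05 with 80% power needs 58 in total when the standardised difference is 0.75. If that corresponded to 7 points, the SD of change would be 7 / 0.75 = 9.3. The article does not say that it did, so 9.3 is an assumption. The step to 70 matches 58 × 1.2 = 69.6.

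**Inputs for the check.** Evaluable patients: 70 × 0.80 = 56, or 28 per arm. True mean difference: 7 points. Alpha: 0.05 two-sided. Assumed: normally distributed change from baseline to T2, SD 9.3, 12 or 16, and mean control change m of 0, −3 or −7.

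**Formulas.**

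- Improver rates: control p_C = 1 − Φ((7 − m)/SD); intervention p_I = 1 − Φ((7 − (m + 7))/SD) = 1 − Φ(−m/SD).
- Fisher power: the sum over all pairs (i, j) of Bin(i; 28, p_I) × Bin(j; 28, p_C), counting the pairs with a two-sided Fisher p ≤ 0.05.
- Comparison of mean change: noncentral t with 54 df and noncentrality (7/SD) × √(28/2). For SD 9.3 this is 0.753 × 3.742 = 2.82; for SD 12 it is 0.583 × 3.742 = 2.18.

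Example, SD 9.3 and m = −7: p_C = 1 − Φ(14/9.3) = 0.066 and p_I = 1 − Φ(7/9.3) = 0.226.

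| SD of change | Control change | Improvers, control vs intervention | Fisher power | t-test power |
|---|---|---|---|---|
| 9.3 | 0 | 0.226 vs 0.500 | 0.48 | 0.79 |
| 9.3 | −3 | 0.141 vs 0.374 | 0.40 | 0.79 |
| 9.3 | −7 | 0.066 vs 0.226 | 0.23 | 0.79 |
| 12 | 0 | 0.280 vs 0.500 | 0.30 | 0.57 |
| 12 | −3 | 0.202 vs 0.401 | 0.28 | 0.57 |
| 12 | −7 | 0.122 vs 0.280 | 0.20 | 0.57 |
| 16 | 0 | 0.331 vs 0.500 | 0.17 | 0.36 |
| 16 | −3 | 0.266 vs 0.426 | 0.17 | 0.36 |
| 16 | −7 | 0.191 vs 0.331 | 0.14 | 0.36 |

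The rows with m = −7 are the purely protective case: intervention patients stay level on average while controls lose 7 points.

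**Sensitivity.**

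- With all 35 per arm evaluable and SD 9.3, Fisher has 0.59, 0.51 and 0.35 for m = 0, −3 and −7, against 0.87 for the t-test.
- With 29 per arm and t-test power of 0.80, even the most favourable split (35% vs 65% improvers) gives Fisher only 0.50. Reaching 80% with the responder comparison would take about 52 to 89 evaluable patients per arm (continuity-corrected), not 29.
- In the same setting, adjusting the continuous comparison for baseline gives 0.85 to 0.90 for baseline correlations of 0.7 down to 0.5.
- Part of the loss is Fisher's conservatism. At 28 per arm its true size is 0.8%, 2.2%, 2.7% and 2.3% at common responder rates of 0.1, 0.23, 0.3 and 0.5, against a nominal 5%.

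**The case against.** The strongest reply is that Fisher's test is one of several planned analyses and nothing calls it primary or decisive. The mixed model and the standardised mean difference are already in Data analysis, and the Abstract promises effect sizes with confidence intervals. The trial calls itself a pilot in the Abstract, and the ranking may be in a statistical analysis plan that is not shown. This stands. The absence of a ranking is not by itself the fault; the two uses of 7 points, and the different accounts in the Abstract and in Data analysis, are in the text as published.

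It is also fair that the listed aims speak of improvement, which an improver count does address. The responder definition is therefore incomplete for a protective aim rather than plainly wrong. It does take baseline into account by subtraction, though not as a covariate.

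A reader might infer more than the article supports:

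- **That Fisher's test is the only intention-to-treat comparison.** The Abstract ties intention-to-treat to the mixed model as well.
- **That a real 7-point benefit would probably be reported as no difference.** That requires the Fisher result alone to decide. Under Study assessments, an observed 7-point group difference would be read as tending towards benefit. At SD 12 even the comparison of means has only 57% power, so part of that risk comes from sample size.
- **That the trial expects controls to decline by a given amount.** No expected control change is stated.
- **That a ceiling on PCI blocks many patients from responding.** A patient within 7 points of the best score cannot respond, but the article gives no PCI range or baseline distribution, so the number affected is unknown.

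**Conclusion.** The point holds in a limited form. The article uses 7 points in two incompatible ways, and the per-patient version is poorly matched to the protective aim. It loses power in every scenario tried. At 28 per arm with a true 7-point difference, the loss is from 79% to 23–48% at SD 9.3, and from 57% to 20–30% at SD 12. These sizes are illustrative, since they rest on normal change scores, assumed SDs and assumed control changes. The direction does not depend on those choices within the range examined. The further fall in Fisher power as controls decline is clear at SD 9.3 and 12, but nearly flat at SD 16.

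The harm to the trial's conclusion is conditional on how much weight the Fisher result is given. This should be fixed before analysis, but it is not a defect that invalidates the trial.

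**What to change.** State one primary intention-to-treat comparison: the between-group difference in continuous PCI at T2 from the mixed model, adjusted for baseline, with a 95% confidence interval, judged against the 7-point between-group criterion in Study assessments. Keep the 7-point improver comparison as secondary. Add the proportion declining by 7 points or more, which speaks to protection. That proportion should stay secondary too: with SD 9.3 and controls falling by 7, the decliner rates are Φ(0) = 0.500 and Φ(−7/9.3) = 0.226, the same pair as in the first table row, so Fisher power is again 0.48 against 0.79. Then bring the Abstract, Study assessments and Data analysis into line.

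The cost is wording only, with no new patients or data. The change should be dated and made before outcomes are compared by arm. The downside is that the easily communicated responder headline becomes secondary.

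### The PCI effect size is defined from post-treatment means without baseline PCI, so it keeps chance imbalance, has a wider interval than necessary, and differs from the mixed-model contrast

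*Protocol article*

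**What the plan says.** The abstract says that the PCI score "as the primary cognitive outcome will be reported descriptively, while effect sizes and 95% confidence intervals (CIs) will be calculated". Data analysis gives the only definition of a between-group effect size: "The between-group effect size will be calculated in post-treatment means (dividing the between-group difference with the pooled standard deviation". The formula has no baseline term, and the result is then graded from small to very large.

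Study assessments places the measurements "at pre-intervention (T0), 8 weeks (T1), and 12 weeks (T2) during intervention", so every randomised patient should have a baseline PCI.

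Two other PCI analyses are planned in the same section. One is a Fisher's exact test on 7-point improvers. The other is a mixed model to "analyze the changes in cognition such as treatment, time point, and the interaction between treatment and time point". No baseline covariate is named for that model. The section also says: "All cases for both baseline and follow-up measurements will be analyzed for the different outcomes". Explicit adjustment for baseline appears only in the regression of cognitive change on symptom change, which is not a treatment comparison. Randomization and blinding describes 1:1 assignment and no stratification on PCI.

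**The concern.** In a trial of about 70 patients the arms can differ noticeably on baseline PCI by chance. A patient's later PCI is likely to be correlated with the baseline value, so part of that difference reappears in the post-treatment means and therefore in the effect size. The baseline score that would remove it, and explain part of the outcome variance, is already collected.

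There is also a mismatch. If the pre-intervention score is one of the outcomes in the mixed model, the treatment-by-time term at 12 weeks behaves like a difference in change scores. The reported effect size and the tested contrast are then different quantities, and baseline imbalance moves them in opposite directions. A reader could see an effect size and a model result that do not agree, with no rule for which to believe.

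**Working it through.** **Inputs from the protocol article.** 70 randomised 1:1 (35 per arm); 58 evaluable for the power calculation (29 per arm); 20% dropout, so 70 × 0.8 = 56 (28 per arm) if it occurs in full; two-sided 0.05. The Sample size section gives no effect size or SD, so everything below is in SD units.

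**Assumptions.** The baseline-to-follow-up correlation ρ is not in the documents and is set to 0.3, 0.5, 0.6 and 0.7. SDs are taken as equal across arms and visits.

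**1. Size of chance imbalance.** The standard error of the baseline difference with 35 per arm is √(2/35) = 0.239 SD. The probability that the arms differ by more than 0.3 SD is 2 × [1 − Φ(0.3/0.239)] = 0.21.

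**2. Where the imbalance goes.** Given a baseline difference b, the expected shift is ρb in the post-only difference and (ρ − 1)b in the change-score difference. It is zero after adjustment for baseline. For b = 0.3:

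| ρ | post-only | change score |
|---|---|---|
| 0.3 | +0.09 | −0.21 |
| 0.5 | +0.15 | −0.15 |
| 0.6 | +0.18 | −0.12 |
| 0.7 | +0.21 | −0.09 |

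The two estimates differ by exactly b. With 29 per arm, b has standard error √(2/29) = 0.263, so they differ by more than 0.3 SD in about 25% of trials. A simulation of 10,000 trials agrees on direction. The correlation of the estimate with baseline imbalance was 0.28, 0.50 and 0.69 for post-only and −0.60, −0.51 and −0.39 for change at ρ = 0.3, 0.5 and 0.7. It was about 0 after baseline adjustment.

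**3. Precision of the effect size.** The variance factor for adjusted against post-only is 1 − ρ². With 29 per arm the unadjusted half-width is t(0.975; 56) × 0.263 = 2.003 × 0.263 = 0.53. The adjusted half-width is 0.526 × √(1 − ρ²):

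| ρ | variance cut, ρ² | half-width |
|---|---|---|
| 0.3 | 9% | 0.50 |
| 0.5 | 25% | 0.46 |
| 0.6 | 36% | 0.42 |
| 0.7 | 49% | 0.38 |

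Allowing for estimation of the regression slope adds at most 0.005 (0.507 at ρ = 0.3).

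**4. Gain against the planned model contrast.** If the pre-intervention score is an outcome in the model, the contrast has variance proportional to 2(1 − ρ). Then adjusted/change = (1 − ρ²)/[2(1 − ρ)] = (1 + ρ)/2. The saving is 1 − (1 + ρ)/2, which is 25%, 20% and 15% at ρ = 0.5, 0.6 and 0.7. At 0.3 it is 35%.

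For power, take a true difference of 0.50 SD, 28 per arm and the noncentral t. The effective d is 0.50/√[2(1 − ρ)] for change and 0.50/√(1 − ρ²) for adjusted:

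| ρ | change: d, power | adjusted: d, power |
|---|---|---|
| 0.5 | 0.50, 45% | 0.58, 56% |
| 0.6 | 0.56, 54% | 0.63, 63% |
| 0.7 | 0.65, 66% | 0.70, 73% |

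**The case against.** Four points have force.

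- **No bias.** Randomisation makes the post-treatment difference unbiased. A shift of 0.18 SD is about two-thirds of one standard error (0.27 SD at 28 per arm), and the interval already allows for such sampling error. This stands. It also means that a reader should not infer a biased effect size. The loss is precision, plus an imbalance that will be visible in this trial and could be removed.

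- **The analysis as a whole does use baseline.** A 7-point improvement needs a baseline value, and the mixed model concerns changes. This stands: what omits baseline is the effect size, not the whole plan. One might also infer large power gains by starting from a t-test on post-treatment scores. The protocol plans no such test, so the fair comparison is with the model contrast, and the gain there is 11, 9 and 7 percentage points at ρ = 0.5, 0.6 and 0.7.

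- **The text could mean model-estimated means, and model covariates are often left to an analysis plan that is not shown.** This stands in part. Dividing by a pooled SD points to observed means but does not prove it, and the silence on a model covariate is not itself a fault. The effect-size formula, however, is written out, and it contains no baseline term.

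- **The correlation is unknown.** At 0.3 the half-width moves only from 0.53 to 0.50. This stands and limits any claim about size.

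**Conclusion.** The point holds as an inexpensive improvement to the main reported PCI figure, together with a mismatch that should be removed; it does not invalidate the trial. The effect-size gain is small at a correlation of 0.3 and substantial from 0.5 upwards. Against a change-type contrast the order reverses: the saving is largest at low correlation. Conditioning on baseline is therefore at least as precise as either quantity, apart from the trivial cost of estimating one slope, whichever correlation applies.

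These sizes rest on the assumed correlations, on equal SDs, and, for the comparison with the model, on the pre-intervention score being one of its outcomes. The article suggests that last point but does not settle it. The opposite reaction to baseline imbalance depends on the same condition.

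**What to change.** In Data analysis, replace the effect-size sentence with one that does the following:

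- Estimates the treatment difference in PCI at 8 and at 12 weeks from the linear mixed model, either with those two visits as outcomes and baseline PCI as a covariate, or with all three visits as outcomes and a common baseline mean for the two arms.
- Defines the effect size as that adjusted difference divided by the pooled baseline SD (not the residual SD), with its 95% confidence interval.
- States that the reported estimate and the model test refer to this same contrast.

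The same definition can serve the other continuous outcomes measured before the intervention. The change needs no extra patients, visits or data, only revised wording and the matching model specification, preferably fixed before outcome data are compared by arm.
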